### Study procedures

The study flowchart is presented in Fig. 1. The study timeline is presented in Fig. 2.

**Fig. 1 Fig1:**
[figure not shown]
Study flowchart/CONSORT diagram

**Fig. 2 Fig2:**
[figure not shown]
Time line and procedures

### Intervention

Feasible patients are assessed by the participating study centers and registered to the coordinating trial center. Patients meeting the inclusion criteria and signing a written informed consent are randomized into the study arms. Patients in the intervention group are offered an additional nursing intervention after discharge for 8 weeks. The intervention time-line was adjusted to the actual S3-guideline on the treatment of colorectal cancer regarding the recommended latest onset of adjuvant chemotherapy. The intervention consists of a standardized protocol-based telephone follow-up serving once per week to disclose patients’ current supportive needs and in order to detect therapy-related physical and psychological impairments as early as possible. Standardized protocols were developed beforehand to ensure both consistent assessment and patient information during the counseling. Additionally, the SCAN is at patients’ disposal for contact from the beginning of primary therapy during the inpatient stage to outpatient aftercare for up to eight months. The intervention covers the entire period of transition from acute clinical care to out-patient aftercare.

### Training of the nursing staff

Incidents classified as critical were processed beforehand by the research group into a telephone guideline. These incidents and appropriate counseling facilities are included in the training program prior to the implementation of the intervention. Specialist oncology nurses designated to carry out the intervention underwent a two-day training (a total of 18 h) conducted by clinical oncologists and members of the study group.

### In-patient period

Patients in the intervention group are visited twice by a specially trained oncology nurse (Supportive Cancer Care Networker, SCAN) during their inpatient stay. Both visits take about 30 to 60 min. Fist, patients are given relevant information, i.e. contact with specialists, voluntary services and the next steps and appointments of the treatment plan on the second last day before discharge from hospital. Second, at the last day before discharge the SCAN takes up the contact information and appoints weekly telephone consultations for eight weeks. Patients are handed out written information materials and the study documents, as for example, patient-held records (PHR), are explained. The PHR is derived from a newly generated 37-item generic supportive needs questionnaire “*Fragebogen zur Erfassung von Unterstützungsbedarfen von Tumorpatienten*“(FU-T). To ensure that patients are enabled to inform structured and completely about relevant changes of their medical condition, filling in the PHR is practiced under instructions. In coordination with the treating clinicians, critical events in which an immediate contact to the SCAN should occur are listed individually.

### Out-patient period

During the outpatient intervention period the SCAN inquires therapy-related symptoms and functional limitations of patients regularly using patient-held records (PHR) in order to assist patients during the transition from inpatient acute care to outpatient aftercare. In the first eight weeks after hospital discharge obligatory telephone consultations are carried out by the SCAN. During the consultations the SCAN rates the urgency of unmet supportive needs, incorporates qualified help if necessary and supports communication of involved health care professionals. Support is provided in five categories of possible supportive needs following standardized protocols:Proper self-management strategies for physical and psychological symptomsPatients stating persistent physical or psychological symptoms are guided in effective self-assessment possibilities. Moreover, depending on the kind of symptom suitable self-management strategies are discussed by the SCAN.Warranty of care continuityThe entries in the PHR are discussed on the phone with a SCAN regarding critical incidents. Here, the individually determined critical events and processes are forwarded to attending hospitals or resident physicians in order to initiate treatments appropriate to the occurring problems and to call in or hospitalize patients. Additionally, patients have the possibility to call between telephone appointments in case of therapy-related complications and side-effects and of psycho-oncological or logistic problems. An early detection of therapy-related physical and psychological impairments also aims at optimizing treatment management by providing an almost real time feedback to the medical professionals.Informed decision makingBeginning at the in-patient consultations, detailed information on the therapy plan as well as alternatives is provided. Further information needs are addressed during the appointed telephone calls, depending on the occurrence of events in need for support, e.g. pharmacological and non-pharmacological supportive measures, or referred to qualified external health care professionals and self-help groups.ParticipationIn addition, within the entire out-patient intervention period, patients are guided in access to office-based oncology specialists and organizational or logistical barriers to medical treatment facilities are discussed with the SCAN. Furthermore, patients are actively encouraged to keep a high therapy adherence, especially in patients living in rural areas or the socioeconomically deprived.Psycho-social well-beingThe consultation is aimed individually on the patient. Counseling on psychological well-being pursues an improvement of the quality of life by the support of the psychic as well as the social functionality of the patient, which is possibly a prognostic factor for the overall survival [10, 27]. Thereby, special attention is paid to individual resources of the patients. Patients are aided in defining both useful individual and institutional resources, e.g. experiences of self-efficacy or available social security benefits.

### Follow-up

In order to determine differences in healthcare services utilization between intervention group and controls, all patients are asked to fill out additional written questionnaires at 8 weeks and 8 months after discharge from hospital. At both times, patient’s adherence to medical recommendations and completion of medical therapies is assessed as well.

### Potential adverse events

The SCAN intervention with a non-invasive educational profile is considered to include no additional risk.

### Removal from the study

Subjects may refuse to participate in the study at any time without giving a reason. The following further reasons can lead to withdrawal of the study for single patients:Wish of the patient,non-compliance,Not the predictable health disturbances which force the patient to the withdrawal, according to the appraisal of the treating doctor,Death of the patient.

### Statistics

#### Primary endpoint analysis

The analysis of the primary outcome will obey to the intention-to-treat principle using generalized linear regression modelling and reported as relative risk with its according 95 % confidence interval. The model will be adjusted for cancer site, tumor stage, cancer therapy, ECOG performance status, age, sex and eventual previous neoadjuvant radiation therapies.

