### Primary endpoint

The effectiveness of SCAN program will be assessed on an individual patient level by comparing the proportion of patients who achieved a clinical relevant improvement of their HRQoL by 10 pts. At 8 weeks after discharge from hospital.

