### Secondary endpoints

An overview on primary and secondary endpoints and the study timeline is provided in Table 1:

**Table 1 Tab1:** Outcome measures and measure times

Measure times		T0	T1	T2
Outcomes & Instruments		Baseline (day before discharge)	Primary measurement (8 weeks after discharge)	Follow-up (8 months after discharge)
HRQoL (primary outcome)	EORTC QLQ-C30 + EORTC-QLQ CR29	x	x	x
Utilization of adjuvant chemotherapy			x (if appropriate)	x
Supportive Care Needs and individual resources	FU-T 37		x	x
Distress	Distress Thermometer (DT)		x	x
Symptoms and functional impairments	MD Anderson Symptom Inventory		x	x

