### Sample size

For sample size calculation the portion of the patients who reach a clinically relevant improvement of the global health-related quality of life (HRQoL) within 8 weeks after discharge from hospital is chosen. The sample size calculation is based on an expected response difference of 15% points in the subscale *“global health status”*/QoL of QLQ-C30 EORTC between the intervention and the standard treatment 8 weeks after the clinic dismissal after surgical therapy. Own reference data [30] show a response of 48 % in standard treatment, so that in the intervention group responses of 63 % are expected. To be able to detect a relevant effect of the intervention with a rise of the responses by 15% points with 80 % power, *n* = 370 patients (*n* = 185 patients per study arm) are needed. Including a dropout rate of approx. 10 %, *n* = 406 patients (*n* = 203 per study arm) will be recruited.

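### The primary model leaves out the baseline global health score, although responder status is calculated from it and the trial already collects it

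*Protocol article*

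**What the plan says.** The section on the primary endpoint defines success for each patient by "comparing the proportion of patients who achieved a clinical relevant improvement of their HRQoL by 10 pts", assessed 8 weeks after discharge. The Sample size section identifies the scale as global health status/QoL of the QLQ-C30: "The sample size calculation is based on an expected response difference of 15% points in the subscale" of that name. Table 1 lists "EORTC QLQ-C30 + EORTC-QLQ CR29" at T0, T1 and T2, with T0 on the day before discharge.

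Under Primary endpoint analysis, a generalised linear model is to give a relative risk with a 95% confidence interval, and the covariates are named: "The model will be adjusted for cancer site, tumor stage, cancer therapy, ECOG performance status, age, sex", with previous neoadjuvant radiation as the last item. The T0 score is not among them. The Randomization section stratifies by centre only.

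**The concern.** Response requires the 8-week score to exceed the T0 score by at least 10 points, so T0 is part of the outcome definition. On a 0–100 scale a patient who starts above 90 cannot respond, and one who starts low is helped by regression to the mean. T0 is therefore likely to predict response more strongly than any listed covariate.

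Subtracting T0 does not adjust for it. With equal standard deviations at both times and correlation ρ, the correlation of change with T0 is −√((1−ρ)/2): −0.63 at ρ = 0.2, −0.50 at 0.5 and −0.39 at 0.7.

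Two things are at stake. A chance difference in T0 between the arms carries over into the responder comparison. The confidence interval for the relative risk is also wider than the data allow. This is not a detail left for a later document, because the article names its adjustment set and this variable is not in it.

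**Working it through.** **1. The plan's own figure.** Inputs from the Sample size section: 48% v 63%, 80% power. Two-sided α of 0.05 is assumed, in line with the 95% interval.

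- Uncorrected n per arm = [1.96·√(2·0.555·0.445) + 0.842·√(0.48·0.52 + 0.63·0.37)]² / 0.15² = (1.378 + 0.585)² / 0.0225 ≈ 171.1, so 172.
- With continuity correction: (171.1/4)·[1 + √(1 + 4/(171.1·0.15))]² ≈ 184.2, so 185 per arm and 370 in total.

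The stated 370 is reproduced. It comes from an unadjusted comparison and counts on no gain from covariates. Without the correction, power at 185 per arm is 83.0%.

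**2. Precision without T0.** SE(log RR) = √[0.52/(0.48·185) + 0.37/(0.63·185)] = √(0.00586 + 0.00317) = 0.095.

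**3. Effect of adding T0.** The documents give no T0 mean, standard deviation or correlation with the 8-week score, so these are assumed and varied. Simulation: 1,500 trials of 370 patients per scenario, T0 mean 55, SD 20, scores rounded to steps of 100/12 and held within 0–100, response rates calibrated to 48% and 63%, Poisson regression with robust standard errors.

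| Correlation T0–8 weeks | Control response, lowest / highest T0 quarter | Power without T0 | Power with T0 | SE without | SE with |
|---|---|---|---|---|---|
| 0.2 | 79% / 19% | 83.3% | 89.7% | 0.095 | 0.085 |
| 0.3 | 77% / 21% | 81.4% | 88.5% | 0.095 | 0.085 |
| 0.5 | 72% / 25% | 83.5% | 89.6% | 0.095 | 0.087 |
| 0.7 | 67% / 29% | 86.3% | 87.7% | 0.095 | 0.090 |

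The relative risk stays at 1.31–1.32 with or without T0. Monte Carlo error is about 1 percentage point. Power without T0 should not depend on the correlation, so the spread in that column is mostly noise and the standard errors are the steadier guide.

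A further set (2,000 trials per scenario, SD 22) gave 85.2% to 90.6% at correlation 0.3, 83.7% to 87.4% at 0.4, 81.9% to 87.1% at 0.5 and 81.6% to 86.3% at 0.6. The SE fell from 0.095 to 0.086–0.090. Type I error with T0 in the model was 4.6% at correlation 0.4.

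**4. In terms of patients.** The equivalent gain is (SE without / SE with)² − 1:

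- (0.095/0.090)² = 1.11, so 11%
- (0.095/0.086)² = 1.22, so 22%
- (0.095/0.085)² = 1.25, so 25%

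**5. Check without simulation noise.** Power ≈ Φ(ln(0.63/0.48)/SE − 1.96), with ln(1.3125) = 0.272:

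- SE 0.095: Φ(0.90) = 82%
- SE 0.090: Φ(1.06) = 86%
- SE 0.085: Φ(1.24) = 89%

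**6. Chance imbalance.** With SD 22, the standard deviation of the between-arm difference in mean T0 is 22·√(2/185) = 2.3 points, and the 95% limit is 1.96·2.3 = 4.5 points. With no true effect and a correlation of 0.4, an imbalance of 4.5 points moved the responder difference by about 4 to 5 percentage points. In the SD 20 simulations an imbalance of one standard deviation (about 2 points) moved the log relative risk by 0.034–0.051, or about 3–5% of the relative risk.

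**The case against.** The strongest reply is that nothing in the plan fails. Randomisation makes the analysis unbiased on average without T0. The ordinary confidence interval already allows for chance imbalance. The 80% target is met by an unadjusted comparison, so the power lost is surplus. All of that is correct, and it limits the point to efficiency and robustness.

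Three further limits also stand:

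- The 4.5-point imbalance is the edge of the 95% range. The mean absolute imbalance is 0.80·2.3 ≈ 1.8 points. Scaling the lower estimate of the shift in proportion gives 4·1.8/4.5 ≈ 1.6 percentage points, against a target of 15.
- The gain shrinks at a high correlation. At 0.7 the simulated power gain was between about 1 and 4 points across runs. The simulations also leave out the listed covariates, some of which, such as ECOG status, may recover part of the benefit.
- That T0 is the strongest predictor is inferred from how the endpoint is built. No figure in the article shows it.

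A separate objection concerns timing. Table 1 puts T0 on the day before discharge, while the In-patient period section places the first nurse visit on the day before that. T0 as scheduled may therefore follow randomisation and first contact with the intervention, and adjusting for it could condition on a post-randomisation value. This affects how T0 should be collected. It is no reason to omit T0, because the endpoint already subtracts the same measurement and any contamination is already in the outcome.

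**Conclusion.** The concern holds. The protocol fixes a covariate list without the baseline value of the variable whose change defines the primary endpoint, and nothing else in the design balances it. At 370 evaluable patients and 48% v 63%, including T0 would cut the variance of the log relative risk by about 10–20% and raise power by roughly 1 to 7 percentage points. It would also remove the linear part of any chance T0 imbalance. These sizes rest on an assumed T0 SD of 20–22 and correlations of 0.2–0.7. The direction follows from the change-based definition and was the same in every scenario. This is a recommended improvement and not a fault that invalidates the planned analysis.

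**What to change.** Add the T0 QLQ-C30 global health status score, as a continuous covariate, to the prespecified primary model, and record the change before any comparison of outcomes by arm. Naming it in advance also avoids a dispute over post hoc adjustment if the arms turn out to differ at baseline.

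The T0 used should be collected before randomisation and before the first nurse visit. Where the questionnaire is already completed by then, the cost is one line of analysis-plan wording, with no extra patients, visits or data items. Where it is not, the questionnaire must be moved earlier for patients still to be enrolled. For patients already enrolled, the timing of T0 relative to randomisation should be reported.

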## Methods/Design

### Study design

SCAN is a prospective randomized controlled multi-center trial in adult patients with colorectal cancer (International Classification of Diseases, ICD-10 C18-20) in Union internationale contre le cancer (UICC) stage I-III. The study is conducted in the surgical wards of eight large and middle-sized cancer centers and general hospitals in Saxony-Anhalt and Saxony, Germany.

Patients randomly assigned to the intervention arm receive additional support by specially trained oncology nurses for eight weeks after discharge from hospital following surgical therapy. Allocation to either intervention or control group is performed with equal ratio. The following amendments were submitted to the local ethics committee and approved on June 4^th^ 2013:Expansion of eligibility criteria to UICC stage I andChange of the primary outcome from adjuvant chemotherapy utilization to HRQoL.

Both amendments are causally linked to one another. Prior to the amendment only patients with UICC stage II & III were eligible for trial inclusion because of the actual medical guideline for the treatment of colorectal cancer. According to this guideline, adjuvant chemotherapy is indicated in patients with UICC stage II and more advanced tumor states only. Due to upcoming effects of the establishment of the preventive colonoscopy as a standard benefit of the German statutory health insurance a noticeable shift regarding tumor stages is obvious. Studies, which were published after approval of the study by the sponsor show that colorectal cancer, despite of the low participation rate of the healthy general population is detected significantly more often in early stages (UICC I) [36, 37] than previous reference data suggested. Nevertheless, this positive effect leads to a significant reduction of the patients eligible for the study. With the additional inclusion of patients in the UICC stage I a rise of the case number of approx. 40 % could be achieved. At the same time, patients in UICC I are not indicated to adjuvant chemotherapy. As a result, widening the eligibility criteria had to be accompanied by changing the primary outcome. Since HRQoL had been defined as a central secondary outcome, the primary outcome was replaced by a former secondary one without changing elements or procedures of the intervention itself.

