### Randomization

Randomization on an individual level, patient enrollment and group allocation will be performed by fax from the Institute of Medical Epidemiology, Biostatistics, and Informatics (IMEBI), Halle as an external and independent unit. Randomization will be stratified by center using blocks of variable length from a reproducible SAS PROC PLAN code. A consecutive analysis of non-responders and of the causes for changes in therapy regimes is intended additionally due to the high therapy-related impairments in wellbeing and quality of life during adjuvant chemotherapy.

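### Centre stratifies the randomisation but is missing from the primary model's covariate list, so the reported standard error is mildly too large if response differs between centres

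*Protocol article*

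**What the plan says.** In the protocol article, the Randomization section states: "Randomization will be stratified by center using blocks of variable length from a reproducible SAS PROC PLAN code". No other stratification factor is named. The Study design section places the trial in the "surgical wards of eight large and middle-sized cancer centers and general hospitals" of two federal states, with 1:1 allocation.

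The Primary endpoint analysis section sets an intention-to-treat comparison "using generalized linear regression modelling and reported as relative risk with its according 95 % confidence interval", and continues: "The model will be adjusted for cancer site, tumor stage, cancer therapy, ECOG performance status, age, sex and eventual previous neoadjuvant radiation therapies". That makes seven covariates, all describing the patient, the tumour or its treatment. No section brings centre in by another route, such as a fixed or random effect, a stratified estimator or a variance that reflects the stratified allocation.

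**The concern.** Blocking within centre keeps the arms nearly balanced in each hospital, so differences between hospitals largely cancel from the treatment contrast. A model without centre does not know this. It counts between-centre variation as error and reports a standard error suited to unstratified allocation. If centres differ, that standard error is larger than the real sampling variability of the estimate.

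At stake are the width of the reported interval and the sensitivity of the test. The trial is planned at 80% power, so any power given up this way is avoidable. Centre differences are conceivable, because the sites mix cancer centres and general hospitals of different size and no listed covariate represents the site itself.

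**Working it through.** **1. The plan's own figure.** Inputs from the Sample size section: 48% response in standard care, 63% with the intervention, 80% power. Alpha is not stated; I assume two-sided 5%, in line with the 95% interval.

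- Uncorrected: n' = [1.960·√(2·0.555·0.445) + 0.842·√(0.48·0.52 + 0.63·0.37)]² / 0.15² = (1.3775 + 0.5847)² / 0.0225 ≈ 171.1, so 172 per arm.
- Continuity-corrected: n = (n'/4)·[1 + √(1 + 4/(n'·0.15))]² ≈ 184.2, so **185 per arm, 370 in total**, as stated.

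This is an unstratified two-proportion formula. Accounting for centre does not alter it.

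**2. Standard error without centre.** SE(log RR) = √[(1−p₁)/(n·p₁) + (1−p₀)/(n·p₀)] with n = 185:
- null (both 48%): √(2·0.52/88.8) = 0.108
- planned effect: √(0.37/116.55 + 0.52/88.8) = 0.095

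These values hardly depend on how response varies between centres.

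**3. Actual sampling error under within-centre blocking.** Within-centre binomial variance averages p(1−p) − Var(p_k), where p_k is the response in centre k. So actual SE ≈ reported SE · √[1 − Var(p_k)/(p(1−p))]. The gap depends entirely on Var(p_k), which the documents do not give.

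**4. Simulation over an assumed range.** 370 patients; eight centres of 10 to 90 patients (assumed); 1:1 blocks of 4 and 6 within centre; overall response 48% and 63%; 8,000 trials per setting. The crude log RR is compared with a centre-stratified Mantel-Haenszel log RR. The seven planned covariates are not included.

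| Assumed logit SD | Control response across centres (approx.) | Type I error, without → with centre | Power, without → with centre | Reported / actual SE without centre, null | Same, planned effect |
|---|---|---|---|---|---|
| 0 | 48% | 5.2% → 5.0% | 82.8% → 82.5% | 0.1087 / 0.1092 | 0.0954 / 0.0958 |
| 0.3 | 38–62% | 5.2% → 5.2% | 83.3% → 83.2% | 0.1088 / 0.1092 | 0.0953 / 0.0948 |
| 0.5 | 32–71% | 4.9% → 5.1% | 83.5% → 84.4% | 0.1087 / 0.1074 | 0.0954 / 0.0935 |
| 0.8 | 17–75% | 4.0% → 5.1% | 84.8% → 87.2% | 0.1088 / 0.1022 | 0.0953 / 0.0897 |

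Monte Carlo error of a 5% rejection rate is √(0.05·0.95/8000) ≈ 0.24 points.

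- Without centre, the reported SE under the null is too large by about 1% at SD 0.5 (0.1087/0.1074) and 6% at SD 0.8 (0.1088/0.1022).
- With centre, the actual SE is practically the same (planned effect: 0.0935 and 0.0896), and the reported SE matches it to within about 2%.
- Check at SD 0.8: the effective critical value is 1.96·0.1088/0.1022 = 2.087, a two-sided tail of about 3.7%, close to the simulated 4.0%. By step 3, Var(p_k) ≈ [1 − (0.1022/0.1088)²]·0.2496 ≈ 0.029, so centre response rates would have an SD of about 17 percentage points.

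**5. A second estimator.** Modified Poisson with robust SE, equal centres, 2,000 trials per setting, probit SD 0.5 (roughly logit 0.8): reported SE 0.0960 → 0.0897, power 86.0% → 88.5%, type I error 3.9% → 5.5% (Monte Carlo error about 0.5 points). The direction and size agree.

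**6. Control run with no centre variation.** Modified Poisson, near-equal centres, 4,000 trials per setting: adding seven centre indicators still lowers the mean robust SE by about 1% (0.0954 → 0.0945 with the planned effect; 0.1085 → 0.1075 under the null), while the empirical SD stays at 0.0958 with the planned effect. That part is small-sample shrinkage of the robust variance and no gain in information.

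**The case against.** **The plan errs on the safe side.** This is correct. Omitting centre causes no bias and no excess of false positives. A reader might infer that the estimate itself loses precision, but with 1:1 blocks within centre its sampling variability is nearly the same either way. Only the reported standard error, interval and test are affected.

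**A visible effect needs large centre differences.** This also stands. At logit SD 0.3 nothing measurable happens. The 4.0% type I error needs control response running from roughly 17% to 75% across hospitals in two neighbouring states, and the documents neither support nor exclude that. A reader might also take the whole fall in reported SE when centre is added as recovered precision. With modified Poisson at probit SD 0.2 that fall is about 2% (0.0954 → 0.0936), and about half of it appears even when centres do not differ.

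**The calculations are not the planned analysis.** They leave out the seven covariates. If hospitals differ mainly in case mix or therapy, these would absorb part of the effect, so the figures may be too high.

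**An article condenses, and the analysis plan may deal with centre.** This carries some weight, but the article does not leave the model open. It gives an explicit list without the one factor that the randomisation uses. An analysis plan that follows the list keeps the omission, and one that adds centre departs from the published list.

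**Conclusion.** The point holds in a limited form. The primary model as published does not account for the groups within which patients are randomised. If centres differ in response, the interval is somewhat too wide and the test mildly conservative. The size ranges from nil to a type I error of about 4.0% and about 2.4 points of power at logit SD 0.8. It rests on an assumed between-centre variation, assumed centre sizes, a two-sided 5% level and omission of the seven covariates. The documents do not support the inference that the trial is undersized or its primary test invalid. The correction is worth making because it is specific and nearly free.

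**What to change.** Add centre to the covariates of the primary model, and fix this in writing before any outcome data are examined, since a later addition would look data-driven. Use fixed centre indicators by default. State in advance what happens if some centres recruit few patients: either a random intercept for centre, or pooling of small centres by a pre-set rule.

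No extra patients or data are needed, because centre is already used at randomisation. The cost is up to seven parameters (eight centres less one) against about 205 expected responders (370 × 0.555), in a model that already carries seven covariates. If a robust variance is used, it will read about 1% low in SE because of the added terms; a small-sample variance correction, named in advance, deals with this.
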